### Trial design and study setting

The Treatment of impulsivity in adults with probiotics (PROBIA) trial is designed as a 10-week multicenter, prospective, randomized, double-blind, placebo-controlled, parallel design study. It will be performed in close cooperation between three European clinical centers: Goethe University Hospital Frankfurt (Department of Psychiatry, Psychosomatic Medicine and Psychotherapy), Frankfurt, Germany; Vall d’Hebron Research Institute (Psychiatry, Mental Health and Addictions Group), Barcelona, Spain; and Semmelweis University (Department of Psychiatry and Psychotherapy), Budapest, Hungary. These centers are all affiliated with or part of university hospitals and, with around 300 new inpatients and outpatients visiting each center every year, are considered as reference centers for the treatment of ADHD, BPD, and other disorders characterized by high impulsivity levels.

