### Study population and recruitment

Participants will be eligible for participation in this study if they meet all the inclusion criteria and none of the exclusion criteria listed in Table 1. With the aim of gender balancing the study, at least 30% female participants will be included.

**Table 1 Tab1:** Inclusion and exclusion criteria of the PROBIA trial

Inclusion criteria	Both males and females aged 18–65 years
	A high level of multidimensional impulsivity based on both a Clinical Global Impression–Severity Scale (CGI-S) score ≥ 4 and an Affective Reactivity Index (ARI) ≥ 5
	DSM-5 criteria for attention deficit/hyperactivity disorder (ADHD) and/or borderline personality disorder (BPD) confirmed by a structured diagnostic interview (ADHD: Diagnostic Interview for Adult ADHD [DIVA 2.0]; BPD: Structured Clinical Interview for DSM-IV [SCID-II])
	Deemed reliable and compliant with the protocol by the investigator
	Ability to speak and comprehend the native language of the country in which the assessments take place
	Informed consent signed
Exclusion criteria	Antibiotherapy within the last 6 weeks prior to study
	Currently taking probiotics
	Presence of a major psychiatric disorder with psychotic symptoms or other major psychiatric conditions requiring hospitalization (e.g., significant mood disorders)
	Neurological disorders involving central functions (e.g., epilepsy, multiple sclerosis, narcolepsy)
	Intelligence quotient (IQ) < 70 (measured by WAIS, if available)
	Major physical illnesses of the cardiovascular, endocrine, pulmonal, immune, or gastrointestinal system or undergoing immunosuppression
	History of/present clinically relevant somatic acute or chronic disorders that, in the opinion of the investigator, might confound the results of tolerability/safety assessments or prohibit the patient from completing the study or would not be in the best interest of the patient
	Documented allergy, hypersensitivity, or intolerance to any of the ingredients of the intervention
	Subject has taken another investigational product or taken part in a clinical study within 30 days prior to entering the study.

*Abbreviations: DSM Diagnostic and Statistical Manual of Mental Disorders*, *PROBIA* Treatment of impulsivity in adults with probiotics, *WAIS* Wechsler Adult Intelligence Scale

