Trial-specific assessments will be done at T0 (duration, approximately 3 h), scheduled within 1 week after TS. During the week between TS and the baseline visit (T0), the mobile health system will be used at home. Here and during 24 h, participants will wear movement sensors on two working days and on Saturday and Sunday, and they will be asked to complete three 24HDRs on a web-based tool or paper on two nonconsecutive weekdays and one weekend day (duration, 15 min each). Individuals will also be asked to collect feces on one day during the 1-week period at home and to bring it along at T0.

In addition to responding to the questionnaires and scales listed in Table 1, participants will be instructed on how to store and eat the study product (SF or placebo). The intervention will begin on the day after T0, and participants will be asked to continue with their usual medications and/or treatments. Participants will have to complete another three 24HDRs, collect their feces before the next visit, and bring it along at T1, following the same guidelines as during the screening assessments.

T1 (midintervention assessment; duration, approximately 3 h) will take place 5 weeks after T0. This midintervention assessment aims at obtaining the primary and secondary outcome measures during the ongoing trial. Participants will be asked once again to wear movement sensors, complete another three 24 HDRs, and collect their feces 1 week before T2 and bring it along at T2. At 10 weeks after initiating the probiotic or placebo intervention (T2), primary and some secondary outcome measures will be assessed again (duration, approximately 3 h).

Within 1 week after T2 and with the aim of measuring safety aspects of the intervention (i.e., somatic complaints/side effects as well as gastrointestinal symptoms), the follow-up (T3) assessment will take place (duration, approximately 20 min).

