### Statistical analysis

Primary outcome measures will be analyzed by applying logistic regression analyses with type of treatment, diagnostic group (e.g., ADHD, BPD, or both), gender, and center as independent variables. A sample size of 180 participants will allow for detection of an odds ratio of 2.55 with 90% power, assuming a response rate of 20% for the CG at a significance level of 0.05. For simplification purposes, calculations will assume no effects of the covariates on the response rate. Secondary analyses will be performed on the secondary outcome measures assessed at the different time points. General linear models will be applied to examine effects of treatment group on continuous outcome variables while controlling for baseline assessment, gender, diagnostic group, and center. Categorical outcome measures will be investigated using generalized linear models. Treatment effects and their 95% confidence intervals will be reported. To investigate potential long-term effects of probiotics, data of the EG for 10 weeks will be analyzed. General linear models for repeated measurements will be applied to study changes from baseline to follow-up visit for this group, and missing data will be handled by the last observation carried forward method. Statistical significance will be defined at the 0.05 level.

Once the primary and secondary outcome measures results are obtained, all responsible investigators at all study sites will get access to the data to be able to reanalyze the data regarding specific additional research questions.

In case of an external request for replication, the respective statistical analysis will be provided by the trial statistician.

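### The long-term effects analysis tests change in the synbiotic arm alone during the placebo-controlled weeks, so it cannot separate a product effect from placebo response and natural course

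*Protocol article*

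**What the plan says.** The last analysis in the Statistical analysis section of the protocol article has a causal aim and a single-arm data set: "To investigate potential long-term effects of probiotics, data of the EG for 10 weeks will be analyzed". The model follows: "General linear models for repeated measurements will be applied to study changes from baseline to follow-up visit for this group". Missing data are to be handled by last observation carried forward, and significance is set at the 0.05 level. The control group does not enter.

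The Trial design and study setting section describes a "10-week multicenter, prospective, randomized, double-blind, placebo-controlled, parallel design study". No extension phase is described. Table 3 gives one visit schedule for all participants: T0 (week 1), T1 (week 5), T2 (week 10) and T3 (week 11). The Participant timeline section names T0 as the baseline visit and places T3 "Within 1 week after T2 and with the aim of measuring safety aspects of the intervention". Table 3 heads the treatment-phase visits as open label, although the title, the Abstract, and the trial design and randomization sections all describe a double-blind trial.

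The same Statistical analysis section states the sample size "assuming a response rate of 20% for the CG at a significance level of 0.05". It also plans between-arm analyses: logistic regression for the primary outcome, and baseline-adjusted models by treatment group for the secondary outcomes.

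**The concern.** A statement about effects of the product needs a comparison with what would have happened without it. Change from baseline in one arm contains the product effect, if any, plus placebo response, the natural course of symptoms and the effect of usual treatments, which participants continue. Single-arm analysis can be unavoidable in an uncontrolled extension. Here a concurrent randomized control group is observed at the same visits and is set aside.

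The label is a second problem. The period analysed is the main treatment period, with at most one further week, so a long-term conclusion has no data behind it.

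At stake is a significant result for long-term effects of probiotics in a trial whose randomized comparison shows nothing.

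**Working it through.** The plan gives no figure for this analysis. Its power statement concerns the primary between-arm comparison and is not used here, except for the 20% control response and the total of 180.

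**1. Period, visits and arms**

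| Item | What the protocol article gives |
|---|---|
| Data analysed | EG only, 10 weeks; change from baseline to the follow-up visit (Statistical analysis) |
| Controlled phase | 10 weeks, randomized and placebo-controlled (Trial design and study setting) |
| Control data | Same T0 to T3 schedule for both arms (Table 3) |
| After the controlled phase | T3 only, one week after T2, for safety (Participant timeline) |

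The analysis window is the controlled phase, and nothing in the design forces the control group out. The two sentences of the plan also disagree on the endpoint: 10 weeks points to T2, while the follow-up column of Table 3 is T3 at week 11. At T3 the table marks only CGI-I, ARI-S, somatic complaints and the Bristol Stool Scale. Of these, only ARI-S and the Bristol Stool Scale are also marked at T0. For most secondary scales a change from T0 to T3 is therefore not scheduled.

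**2. What the single-arm contrast estimates**

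Let τ be the synbiotic effect on mean change and δ the mean change that would occur without it.

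- EG-only contrast: expected value δ + τ.
- EG minus CG: expected value (δ + τ) − δ = τ.

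With τ = 0 the EG-only test is a test of δ. It holds its 5% level as a test of treatment only if δ = 0. The plan does not expect control patients to stay unchanged: at its own 20% response rate, 0.20 × 90 = 18 of 90 EG patients would respond with an inert product.

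**3. Size, as an illustration**

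Inputs: n = 180/2 = 90 in the EG (1:1 allocation); two-sided 0.05 (the article does not state sidedness); τ = 0; δ = d SDs of the change score, with d assumed because the article gives no SD or expected mean change.

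Method: paired t-test, noncentrality d√n, 89 degrees of freedom, critical value 1.987. The chance of significance is P(|T| > 1.987).

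| Assumed d | Noncentrality | Chance of p < 0.05 with no product effect |
|---|---|---|
| 0 | 0 | 5% |
| 0.1 | 0.95 | 15.5% (about 16%) |
| 0.2 | 1.90 | 46.7% |
| 0.3 | 2.85 | 80.4% |

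If only 72 EG patients were analysed (an assumed 20% loss), the last three rows become 13%, 39% and 71%. An EG-versus-CG test stays at 5% in every row, because δ cancels.

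**4. Regression to the mean**

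Patients are selected on CGI-S and ARI at screening (TS), and both scales are measured again at T0. In standardized scores with equal variances, let λ be the mean selected score at TS, and r₀ and r₂ its correlations with the T0 and T2 scores. The expected scores are r₀λ at T0 and r₂λ at T2, so the expected fall from T0 to T2 is (r₀ − r₂)λ. This is zero if the correlations are equal, and small unless the correlation falls clearly with time. Most other secondary scales are not selection variables.

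**The case against.** The strongest reply is that the control group is not lost. The plan already compares arms on the primary outcome, and on secondary outcomes at the different time points with baseline adjustment and 95% confidence intervals. A null randomized result would be reported beside the EG-only result. This stands, and it confines the harm to one conclusion. It does not rescue that conclusion, because the analysis is set up to investigate effects of the product and cannot do so.

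It is also fair that the percentages rest on assumed values of d. The 20% response is a rate on a composite endpoint and cannot be converted into SDs of change on other scales, and a paired test at two time points is simpler than the planned repeated-measures model. The figures show direction and sensitivity; they are not an estimate for this trial. They count as false positives only when the within-arm change is credited to the product, which is what the stated aim invites.

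Three stronger readings might be inferred, and the document does not support them:

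- **Regression to the mean as a main driver.** Selection is at TS and the Participant timeline section names T0 as baseline, so most of it would precede baseline. It is at most a minor contributor.
- **Carrying forward would copy T2 values into T3.** The rule is stated for missing data. A scale not scheduled at T3 is not missing there, and the 10-week wording points to T2. What stands is that the endpoint visit is unclear.
- **The open-label heading shows that the analysis belongs to another design.** That is a guess about drafting. The heading is simply a contradiction to be corrected.

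**Conclusion.** The point holds in a limited form. As written, the plan tests for long-term effects of the product using change in one arm during the randomized placebo-controlled phase. The result would mix any synbiotic effect with placebo response and natural course, and the data reach no further than one week after treatment. With no product effect, the chance of significance exceeds 5% whenever the non-specific mean change is not zero: about 16%, 47% and 80% for assumed changes of 0.1, 0.2 and 0.3 SD with 90 patients and a two-sided paired test. The direction needs no assumption about SDs; the size depends on them entirely.

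A reader might infer that the trial's efficacy inference is compromised. It is not: the primary and main secondary analyses compare the randomized arms. This is a point that should be fixed, confined to the long-term conclusion, together with the misnamed period, the unclear endpoint visit and the Table 3 heading.

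**What to change.** - Replace the EG-only test with a repeated-measures model on both arms: adjusted for baseline, with treatment, visit and treatment-by-visit terms over T1 and T2. Add T3 only for outcomes scheduled there, such as ARI-S. Report between-arm differences with 95% confidence intervals.
- Keep change within the EG as a descriptive summary, without a claim of effect.
- Drop the long-term label; describe the 10-week course and, where measured, the week after treatment.
- State whether the endpoint is T2 (week 10) or T3 (week 11).
- Reconcile the open-label heading in Table 3 with the double-blind design.

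The cost is analysis wording and one table heading. The visits are already scheduled in both arms, and the sample size does not change.

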### Randomization and study intervention

After eligibility checks have been conducted and written consent has been obtained by the different psychiatrists and/or psychologists of the trial team, eligible participants will be randomized to the experimental (EG) or the control (CG) group in a 1:1 allocation ratio using an independent web-based computerized service (www.randomization.com). Randomization will be center-stratified and have a fixed length per center, being independent of participant characteristics. However, due to the large sample size, a balanced ratio of baseline characteristics between the EG and CG is expected.

Individual participant treatment kits will contain all required daily synbiotic or placebo envelopes for the 10-week RCT and will be prepared in advance by sequentially numbering and labeling them as “A” or “B.” Because this is a double-blind study, neither the participants nor the clinicians involved in the trial will have access to the randomization list.

Synbiotic 2000 Forte 400 (SF) is a synbiotic formula currently produced by Synbiotic AB in Höganäs, Sweden. Each dose (powder-containing sachet) of SF contains 100 billion of each of *Pediococcus pentosaceus* 5-33:3, *Lactobacillus paracasei subsp. paracasei* 19, *Lactobacillus plantarum* 2362, and *Leuconostoc mesenteroides* 77:1, in combination with four bioactive fermentable fibers (2.5 g each of β-glucan, inulin, pectin, and resistant starch). SF is categorized as a generally regarded as safe agent, being tested on several hundreds of critically ill patients (e.g., pancreatitis, liver transplant) with no side effects or specific and/or relevant risks conferred to the trial participants [83]. The placebo (also provided by Synbiotic AB) is composed of the polysaccharide maltodextrin and has a texture and flavor similar to SF. Participants will be asked to continue with their previous medications and/or usual treatments and add the synbiotic or placebo once daily on top of cold foods such as yogurt, muesli, or salad. To secure bacterial viability, participants will be asked to store both SF and placebo at + 4–6 °C.

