### Participant timeline

The trial timeline is shown in Table 3. Time points per intervention will be selected on the basis of known duration to exert effect.

**Table 3 Tab3:** Standard Protocol Items: Recommendations for Interventional Trials (SPIRIT) schematic schedule of enrollment, interventions, and assessments

Study procedures		Screening	Open label			Follow-up
	Visit	TS	T0	T1	T2	T3
	Week	−1	1	5	10	11
	Day	−7 to −1	1	35 ± 2	70 ± 2	77 ± 2
Informed consent form		X				
Inclusion/exclusion criteria		X				
Demographics (including SES)		X				
IQ (IQ score based on WAIS, if available)		X				
M.I.N.I.-Plus assessment		X				
Confirmation of diagnosis/-es		X				
Confirmation of ADHD	DIVA 2.0	X				
Confirmation of BPD	SCID-II	X				
Primary outcome						
Clinical Global Impression–Improvement Scale	CGI-I			X	X	X
Affective Reactivity Index	ARI-S	X	X	X	X	X
Secondary outcomes						
Clinical Global Impression–Severity Scale	CGI-S	X	X	X	X	
Clinician rating of ADHD symptoms	ADHD-RS		X	X	X	
Self-rating of multidimensional impulsivity	UPPS-P		X	X	X	
Questionnaire on well-being			X		X	
Functioning Assessment Short Test	FAST		X	X	X	
Self/other rating of strength and difficulties	SDQ		X	X	X	
Clinician rating of compulsivity	Y-BOCS		X	X	X	
Sleep problems	5-item questionnaire		X	X	X	
Self-rating of emotion regulation difficulties	DERS-16		X	X	X	
Somatic complaints/side effects	Body system questions			X	X	X
Gastrointestinal symptoms	Bristol Stool Scale		X	X	X	X
Self-rating of perceived stress	PSS		X	X	X	
Major stressors			X	X	X	
Blood pressure, pulse rate, height, weight, waist, hip, medical history, medication evaluation	Assessed by clinician		X	X	X	
Physical activity	Actigraphy; mobile health application		X		X	
Blood biomarkers	Blood sample		X	X	X	
Microbiome	Stool sample		X	X	X	
DNA and RNA	Blood sample		X	X	X	
Neurocognitive measures	CPT-II		X	X	X	
Nutritional intake	Food diary		X	X	X	
Treatment adherence/satisfaction/beliefs						
Probabilistic Medication Adherence Scale	ProMAS		X	X	X	

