In the case that a participant’s psychological state deteriorates to a clinically significant degree during the trial, the investigators will either discuss with the participant the possibility of withdrawing from the study or decide that the participant should withdraw. If a participant, for any reason, requires treatment with certain therapeutic agents (i.e., antibiotics), the agent taken and time of administration will be noted. If any other protocol exclusion violation has occurred, the participant’s involvement will be discontinued. Participants may at any time request to be withdrawn from the study or revoke their consent to participate. If a patient is discontinued from the trial, a follow-up visit will be carried out to ensure the well-being of the participant.

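### The EG-only long-term analysis pairs a 10-week data window with a week-11 end point, and LOCF would fill a missed post-treatment visit with an on-treatment score

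*Protocol article*

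**What the plan says.** Two adjacent sentences in the Protocol article, Statistical analysis, define the analysis. The first sets its purpose and its data: "To investigate potential long-term effects of probiotics, data of the EG for 10 weeks will be analyzed". The second sets the model and the end point: "General linear models for repeated measurements will be applied to study changes from baseline to follow-up visit for this group". The same sentence adds that "missing data will be handled by the last observation carried forward method".

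The ten weeks match the treatment period. Under Randomization and study intervention, each participant's kit "will contain all required daily synbiotic or placebo envelopes for the 10-week RCT". The Participant timeline section and its Table 3 put T2 at week 10, day 70 ± 2.

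Follow-up, as a scheduled visit, refers to T3. The Participant timeline says that within a week of T2 "the follow-up (T3) assessment will take place", and Table 3 heads the T3 column as follow-up, week 11, day 77 ± 2. The only other use for a visit is under Criteria for discontinuing allocated interventions, where after a discontinuation "a follow-up visit will be carried out to ensure the well-being of the participant". That visit has no fixed date and cannot be a common time point for a model.

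**The concern.** The two candidate end points answer different questions. Change from baseline to T2 is change while the product is being taken. Change from baseline to T3 is what remains about a week after stopping. A data window that closes at T2 contains no off-treatment time, so it cannot show a lasting effect. A reader of the results could take a T2 finding labelled long-term as evidence of persistence.

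The missing-data rule adds to this if T3 is the end point. A participant seen at T2 but not at T3 would enter T3 with a score taken on treatment. That imputes no change over the one interval in which fading could be seen. As long as the end point is unnamed, the choice between T2 and T3 also stays open until results are known.

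**Working it through.** **Step 1. Dates (Participant timeline, Table 3).**

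| Visit | Week | Day | Status |
|---|---|---|---|
| T0 | 1 | 1 | baseline |
| T1 | 5 | 35 ± 2 | on treatment |
| T2 | 10 | 70 ± 2 | end of treatment |
| T3 | 11 | 77 ± 2 | follow-up |

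Ten weeks is 10 × 7 = 70 days, which is the nominal day of T2. T3 lies 77 − 70 = 7 days later, outside a 10-week window.

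**Step 2. Can the two sentences be read together?**

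- *Ten weeks as length of exposure:* the EG, treated for ten weeks, is followed from baseline to T3. The sentences then agree, but the text does not say this, and long-term would mean about seven days off treatment.
- *Follow-up visit as any post-baseline visit up to T2:* the dates agree, but this departs from the schedule's use of follow-up for T3. The analysis would then cover only on-treatment time and could not address its stated purpose.

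Either way the paragraph needs correcting.

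**Step 3. What each end point can support.** Table 3 lists 2 primary and 20 secondary outcome rows, 22 in all.

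- CGI-I and somatic complaints have no T0 mark, so change from T0 to T2 is available for 22 − 2 = 20 rows.
- Four rows are marked at T3: CGI-I, ARI-S, somatic complaints and the Bristol Stool Scale.
- Two of those four have no T0 value, so change from T0 to T3 is available for 4 − 2 = 2 rows, ARI-S and Bristol.

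For efficacy at T3 this leaves ARI-S as a change score. CGI-I is available only as an improvement rating, which has no baseline by construction.

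**Step 4. Direction of the LOCF bias if T3 is the end point.** Let D be the true mean change from T0 to T2, and L the true mean change from T2 to T3. Let m be the share with a T2 score but no T3 score, and assume that they resemble the others.

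- True change from T0 to T3: D + L.
- LOCF estimate: (1 − m)(D + L) + m × D = D + (1 − m)L.

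The estimated T2-to-T3 change is therefore (1 − m)L, and any fading is understated by the fraction m.

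The documents give neither m nor L. As an illustration only, take m = 5%, 10% or 20% of about 180 / 2 = 90 EG participants. That is 4.5, 9 or 18 carried values and estimates of 0.95L, 0.90L and 0.80L. In scale points the bias is m × L, which cannot be computed without L.

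If T2 is missing too, the carried score comes from T1 or T0. It is still not a post-treatment value, but the direction of the error then depends on the course of scores before T2.

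**The case against.** The strongest reply is that the text is ambiguous rather than contradictory. The first sentence does not name T2 and does not exclude later data, and reading ten weeks as exposure makes the two sentences compatible. That stands in part. A reader might infer a strict contradiction, and the wording does not force one. It does leave the end point unnamed, and the reconciling reading has to be supplied by the reader.

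A second reply is that the LOCF harm is conditional. It needs T3 as the end point, some participants who attend T2 but miss a visit a week later, and an effect that fades in that week. That also stands. The algebra gives a direction under stated assumptions, not a measured size.

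Two stronger readings are tempting and should not be made.

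- Because 18 of the 22 rows (22 − 4) have no T3 mark, a reader might infer that those scales would all be carried forward from T2 and reported as follow-up results. The plan applies LOCF to missing data. A scale never scheduled at a visit is not missing there, and nothing in the article says that such scales would be imputed to week 11.
- The Participant timeline prose describes T3 by its safety purpose and does not mention ARI-S or CGI-I, so a reader might see a conflict with Table 3. The prose is only less complete than the table. Table 3 already schedules both, and no edit is needed there.

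**Conclusion.** The point holds as a minor defect of specification. The stated data window ends at T2, the modelled change ends at a visit that the schedule places at T3, and only an unstated reading joins them. Under either end point, long-term is the wrong label: T2 offers no time off treatment and T3 offers about seven days.

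If T3 is intended, LOCF biases the analysis towards persistence whenever a T2 score is carried forward and an effect fades. The amount is unknown. The 5% to 20% range is an assumption, and the result also rests on those who miss T3 resembling those who attend.

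A reader might infer that the trial's main conclusion is at risk. The documents do not support that. This analysis is secondary and has no control group, and the primary endpoint is assessed at the end of the placebo-controlled phase, T2. The LOCF clause stands in the sentence on the EG-only model, and the point is confined to that analysis.

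**What to change.** In Statistical analysis, name one end point before unblinding.

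**Preferred: T3.**

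- State that change is studied from baseline (T0) to T3 in week 11.
- Limit the change analysis to measures that Table 3 schedules at both T0 and T3. For efficacy this is ARI-S. Report CGI-I at T3 only as an improvement rating.
- Replace LOCF with a likelihood-based repeated-measures model on the observed scores. For ARI-S this can use T0, T1, T2 and T3, with the T2-to-T3 contrast shown beside the T0-to-T3 change, since that contrast addresses persistence directly.
- Describe the result as uncontrolled one-week post-treatment persistence, not as a long-term effect.

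**Alternative: T2.** State that change is studied from baseline to week 10, and drop both the long-term label and the reference to a follow-up visit. Replace LOCF here as well, because it would carry a T1 or baseline score to the end of treatment as if nothing had changed since.

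The cost is a few sentences and a different missing-data method for one secondary analysis. No visit, scale or participant is added, since Table 3 already schedules ARI-S and CGI-I at T3.

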### Outcome measures

#### Primary outcomes

The primary outcome measure will be response to treatment, defined by a reduction in the Affective Reactivity Index–Self-Report (ARI-S) scale total score of at least 30% compared with baseline plus a Clinical Global Impression–Improvement Scale total score of 1 or 2 (very much improved or much improved) at the end of the placebo-controlled phase.

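### Last observation carried forward is fixed for the experimental-group repeated-measures analysis, although participants may be withdrawn because they deteriorate

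*Protocol article*

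**What the plan says.** All references are to the protocol article.

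- **The rule and its place.** The Statistical analysis section introduces an analysis of experimental-group data over the 10 weeks, meant to show possible long-term effects. It continues: "General linear models for repeated measurements will be applied to study changes from baseline to follow-up visit for this group". The same sentence then adds that "missing data will be handled by the last observation carried forward method". No other missing-data rule appears in the article. The sentence on the primary logistic regression has none.
- **Withdrawal.** Criteria for discontinuing allocated interventions deals with a participant who becomes clinically worse in the course of the study. For that situation it says that "the investigators will either discuss with the participant the possibility of withdrawing from the study or decide that the participant should withdraw". A participant may also be discontinued after an adverse event in response to the study product. The one visit promised after discontinuation concerns well-being, and no outcome assessment is mentioned for it.
- **Visits.** T1 "will take place 5 weeks after T0" and is the only on-treatment visit before T2 at week 10. Table 3 labels T3 (week 11) as follow-up. It schedules ARI-S at all five visits and the "Clinical Global Impression–Improvement Scale" (CGI-I) at T1, T2 and T3 only.
- **Primary outcome.** Response needs "a reduction in the Affective Reactivity Index–Self-Report (ARI-S) scale total score of at least 30% compared with baseline" together with a CGI-I "total score of 1 or 2 (very much improved or much improved) at the end of the placebo-controlled phase".

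**The concern.** Carrying the last value forward is sound only if the outcome would not have changed after the participant left. Here the article itself provides for leaving because the outcome has changed for the worse. In those cases the carried T1 value is better than the true later value, and the scheduled visits offer nothing to correct it.

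At stake is the statement about change over 10 weeks in the synbiotic group. The analysis has a single arm, so any error in the filled-in values goes straight into the estimated change. The filled-in values also enter the model as if measured, so standard errors will generally be too small. The article states this method outright, so the point is not about a detail left to a document that is not shown.

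**Working it through.** The article gives no dropout rate and no figure for the effect of missing data, so there is no stated figure to reproduce. The check sets the passages side by side and then uses labelled assumptions.

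**1. Passages side by side.** A participant improves by T1, deteriorates between weeks 5 and 10, and is withdrawn under the discontinuation criteria. The last scheduled observation is T1. The Statistical analysis rule copies T1 to T2 and, for outcomes measured there, to T3. The record shows improvement where the reason for leaving was deterioration. A participant who leaves before T1 has only baseline to carry, so the recorded change is zero.

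**2. Size in the single-arm analysis.**
- Inputs from the article: 180 participants, 1:1, hence 90 in the experimental group.
- Assumed: dropout d of 10%, 20% or 30%, half before T1 and half between T1 and T2.
- Values filled in at T2: 90 × d = 9, 18 or 27.
- Bias in mean improvement = (d/2) × a + (d/2) × b. Here a is carried minus true improvement, on average, in late dropouts, and b is the same in early dropouts.
- If late dropouts are carried one scale unit too well (a = +1) and early dropouts are right (b = 0), the bias is +0.05, +0.10 or +0.15 units.
- If early dropouts would have improved by one unit but are recorded as unchanged (b = −1), the two terms cancel: 0.10 × 1 − 0.10 × 1 = 0 at d = 20%.

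The error from deteriorating withdrawals favours the synbiotic, but neither the sign nor the size of the total can be fixed from the article.

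**3. Only if the rule were also meant for the primary composite.** The text does not say so.
- CGI-I is first rated at T1. With the same assumed dropout, 180 × d/2 = 9, 18 or 27 of all 180 participants would have no CGI-I to carry.
- Article inputs: control response 20%, odds ratio 2.55. Experimental odds are 0.25 × 2.55 = 0.6375, so the rate is 0.6375/1.6375 = 38.9%.
- Let p be the completers' response rate and r the T1 response rate in late dropouts. Further assume that early dropouts are left out under carry-forward. The carry-forward rate is [(1 − d)p + (d/2)r]/(1 − d/2). Counting every dropout as a non-responder gives (1 − d)p.
- Example, d = 20%, r = 20% in both arms: experimental (0.8 × 0.389 + 0.1 × 0.20)/0.9 = 36.8%, control (0.16 + 0.02)/0.9 = 20.0%, odds ratio 2.33. Non-response coding: 31.1% against 16.0%, odds ratio 2.37.

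| d | Carry-forward OR, r = 38.9% / 20% | Carry-forward OR, r = 20% / 20% | Non-response OR |
|---|---|---|---|
| 10% | 2.55 | 2.44 | 2.46 |
| 20% | 2.55 | 2.33 | 2.37 |
| 30% | 2.55 | 2.21 | 2.30 |

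(r is given as experimental / control.) Carry-forward lies above non-response coding in one scenario and slightly below it in the other.

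**4. Unequal withdrawal, under the same condition.** Assume 20% of completers respond in both arms, and a quarter of those withdrawn after T1 were responders at T1 but none responds at T2. With 20% withdrawn in the experimental arm and 10% in control:
- Non-response: 0.8 × 0.20 = 16% against 0.9 × 0.20 = 18%.
- Carry-forward: 16% + 0.20 × 0.25 = 21% against 18% + 0.10 × 0.25 = 20.5%.
- Shift in the difference: 0.25 × (0.20 − 0.10) = +2.5 points. It is 0 with equal withdrawal and −2.5 points with the rates reversed.

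**The case against.** The strongest objection is scope. The rule completes a sentence about one secondary, experimental-group analysis. That analysis has no treatment difference to distort, and CGI-I, which has no baseline rating, cannot be an outcome in a change-from-baseline model. This stands. A reader might infer that the rule biases the primary comparison, that the bias differs by arm, or that everyone lost before T1 falls out of the logistic regression. The document supports none of these. It names neither complete-case analysis nor non-response coding for the primary outcome, and that rule may sit in the full protocol or analysis plan, which are not shown. If baseline ARI-S were carried, an early dropout would show a 0% reduction and count as a non-responder without any CGI-I.

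Differential withdrawal is also undocumented. The active sachet contains live bacteria and 4 × 2.5 g = 10 g of fermentable fiber while placebo is maltodextrin, so it is conceivable. But the article describes the product as tested without side effects.

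The withdrawal passage is permissive as well: investigators may discuss withdrawal or decide on it. Deterioration can therefore lead to missing data but need not.

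Finally, a mixed model or multiple imputation using T1 data also predicts from the good T1 value under a missing-at-random assumption. That is correct, and it is why the fix needs a sensitivity analysis with worse outcomes after withdrawal.

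What the objection does not remove is that the article names a method for this analysis whose assumption conflicts with its own withdrawal criteria.

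**Conclusion.** The point holds for the analysis to which the text attaches the rule. Carrying the last observation forward in the experimental-group repeated-measures model can record a deteriorated, withdrawn participant as improved. It has no comparator to offset the error, and it generally understates uncertainty. The conclusion rests on the wording of the rule, the withdrawal criteria and the visit schedule. Its size and overall direction are unknown, because no dropout rate is given and the figures above depend on assumed rates. The consequences for the primary composite are conditional on an intention that the article does not state. The change should be made, but nothing here shows that the primary analysis is invalid.

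**What to change.** - In the Statistical analysis sentence, replace the carry-forward rule with a likelihood-based mixed model for repeated measures on all observed scheduled visits: T0, T1, T2, and T3 where the outcome is measured, such as ARI-S. Preferably fit it to both arms with a treatment-by-visit term.
- Add a sensitivity analysis that assumes worse outcomes after withdrawal than the model predicts.
- State which analyses the missing-data rule covers. If it was also meant for the primary composite, do not use it there. Analyse all randomized participants, using multiple imputation of ARI-S and CGI-I (then deriving response) and missing counted as non-response, and name in advance which is the main analysis and which the sensitivity analysis.

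The cost is a change of wording and a little more programming. No new visit or measurement is needed.
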